**Figure 4 figure4:**
[figure not shown]
Diagram of trial retention rates.

### Statistical Analysis

We will be analyzing primary outcomes using univariate analyses. The trial retention rate will be measured in terms of the percentage of randomized individuals retained in the intervention at end point assessment and will include a 1-sided 95% confidence interval to estimate the lower bound of the retention rate. CHAMPS acceptability will be reported using univariate analysis. We will also conduct exploratory analyses to test whether belonging to either study arm influenced EIS completion rates.

To describe sociodemographic and clinical variables at baseline, trial parameter data, and secondary and exploratory outcomes, we will conduct univariate analyses. We will use multivariable statistical methods to explore the following outcomes: participant satisfaction, use of cannabis PBS, and motivation to change cannabis PBS. To compare satisfaction between groups, we will use a hierarchical linear regression. The first regression model will insert the intervention arm as the independent study variable; the second model will insert other covariates. We will also conduct a hierarchical linear regression exploring the use of cannabis PBS over time as the outcome; the first regression model will insert study arms as the independent variable, and the second model will insert baseline PBS scores and other relevant covariates. To look at motivation to change, analyses will be done as with cannabis PBS, using hierarchical models that look at RCQ scores as the outcome and control for RCQ scores at baseline.

In multivariable models, we will include sites as random effects and will include certain covariates of interest that differ at baseline. These covariates may include age, sex, gender, study site, education status, employment, housing status, social support, and baseline clinical characteristics including cannabis use and CUD severity. Sensitivity analyses will explore key outcomes in subgroups of participants (eg, location-based subgroups), as well as the use of different thresholds to determine whether participants have completed CHAMPS.

Missing data will be handled issuing guidance of the missing data treatment for each instrument. The proposed analyses will include all participants with at least 1 nonmissing visit. Our analysis plan includes both intention-to-treat and per-protocol analyses.

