### Study Aims

Our team developed a novel harm reduction intervention for individuals with FEP who are interested in reducing their cannabis use–related harms, called the Cannabis Harm–reducing Application to Manage Practices Safely (CHAMPS), which is delivered through a smartphone app. The development of CHAMPS was informed by related projects in cannabis use and psychosis conducted by our team [8,18,26] and co-designed in collaboration with clinicians, patient-partners, and experts in cannabis and psychosis (see intervention description in the Study Arms section). To our knowledge, the CHAMPS intervention represents the first psychosocial mobile health intervention aiming to reduce cannabis use–related harms in people with FEP. Our team is also currently working on a psychosocial mobile health intervention that addresses CUD in people with FEP and focuses on decreasing cannabis use or cessation [27].

Due to the paucity of cannabis harm reduction research in this population, a preliminary assessment of trial feasibility and intervention acceptability as well as an initial assessment of key clinical outcomes were necessary before conducting a large-scale randomized controlled trial (RCT) of CHAMPS [28]. As EIS represent the mainstay of treatment for FEP [29], we opted to evaluate this novel intervention as an adjunctive clinical tool to existing services. We will thus evaluate CHAMPS+EIS versus EIS-only in a multicenter, 2-arm, parallel group, open-label, randomized pilot study. The primary objectives of our study are to assess whether it is feasible to conduct a future RCT of the CHAMPS intervention in people with FEP who use cannabis and want to modify their cannabis behaviors and determine if CHAMPS is an acceptable intervention for this population. Secondary objectives aim to descriptively determine whether CHAMPS+EIS influences the use of protective behavioral strategies (PBS) and motivation to change PBS, compared to EIS only, in young people with psychosis who use cannabis. Exploratory objectives aim to descriptively estimate the effect of the intervention arm on cannabis-related problems, quality of life, cannabis and other substance use, severity of dependence, psychotic symptoms, and health care service use. We hypothesize that CHAMPS will be acceptable to those randomized to the CHAMPS+EIS intervention arm and that the pilot trial will demonstrate adequate feasibility, with a minimum trial retention rate of 60%.

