## Methods

### Participants and Recruitment

This study will involve 100 young adults (50 per arm) who meet the study’s eligibility criteria. Briefly, the inclusion criteria are having a diagnosis of psychosis, being 18 to 35 years old, having recent cannabis use, and being treated at an EIS (see Textbox 1 for detailed inclusion and exclusion criteria). Participants will continue their usual pharmacological and psychosocial interventions offered at the EIS, including taking any medication prescribed for their psychosis or other health concerns while participating in this study; these will be recorded in the patient study file.

If the CHAMPS intervention is considered clinically relevant for a potential participant, a clinician approaches this person, briefly explains the intervention, and asks about any interest in meeting the research team to learn more about the trial. If the person agrees, the referring psychiatrist or clinician collects screening and medical eligibility information. In other words, participant recruitment will use purposive sampling. The research staff then schedules a full screening visit, where eligibility is confirmed, and informed consent is obtained from interested participants (Figure 1; Multimedia Appendices 1 and 2). For study visits conducted via telepsychiatry, e-consent and verification of comprehension are documented using the Research Electronic Data Capture (REDCap; Vanderbilt University) web-based data entry system [30].

Clinicians will assist participants as needed, as they download the CHAMPS app from the Apple Store or the Google Play Store. If potential participants do not own a smartphone, the research staff will loan them a smartphone for the study duration. All participants will receive a compensation of CAD $30 (US $22.14) for participating at each visit (eg, screening, baseline, and follow-up assessment visits), with a maximum of CAD $150 (US $110.69) per participant. In addition, participants randomized to the EIS-only arm are offered CHAMPS access after their trial completion; these data will not be collected for research purposes.

Inclusion and exclusion criteria for participants and recruitment sites.

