### Randomization and Blinding

Participants are randomized in a 1:1 ratio to either arm (EIS-only and EIS+CHAMPS). Randomization is stratified by sex and CUD status using random permuted blocks. The CHUM Center for Integration and Analysis of Medical Data generates the allocation sequence. Access to the randomization code is strictly controlled by the data management team. Individual participant codes can be broken without unblinding the sequence allocation of other participants. Due to the nature of the intervention, clinicians and research staff collecting data cannot be blinded; however, the research staff conducting data analysis are blinded to group assignment. Participants are not able to switch arm assignments.

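### Four exploratory outcomes measured at baseline get univariate analysis only, so their arm differences are estimated less precisely than the data allow (low severity)

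*Protocol article*

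**What the plan says.** Under Study Aims, the article states: "Exploratory objectives aim to descriptively estimate the effect of the intervention arm on cannabis-related problems". The same sentence goes on to substance use, severity of dependence and psychotic symptoms, among others. The aim is therefore a between-arm estimate, expressly descriptive.

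Table 2 (schedule of assessments) has the Marijuana Problems Scale, the Timeline Follow-back, the Severity of Dependence Scale and the Positive and Negative Syndrome Scale (PANSS-6 under Exploratory Outcomes) at baseline and again at weeks 6, 12 and 18.

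The Statistical Analysis section assigns the method: "To describe sociodemographic and clinical variables at baseline, trial parameter data, and secondary and exploratory outcomes, we will conduct univariate analyses". It then says which outcomes are modelled: "We will use multivariable statistical methods to explore the following outcomes: participant satisfaction, use of cannabis PBS, and motivation to change cannabis PBS". None of the four measures above is on that list. For PBS, "the second model will insert baseline PBS scores and other relevant covariates", and the RCQ model likewise controls for its own baseline. Multivariable models carry site as a random effect.

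On design: "This study will involve 100 young adults (50 per arm) who meet the study’s eligibility criteria", and "Randomization is stratified by sex and CUD status using random permuted blocks". None of the four baseline scores is a stratification factor.

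**The concern.** The aim is an arm effect, the baseline scores will be in the database, and the article adjusts for baseline in its two secondary outcomes but not in these four. This is not detail left to a statistical analysis plan: the article names the method for exploratory outcomes and gives a list of modelled outcomes that leaves them out.

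A participant's own baseline score is usually the strongest available predictor of the follow-up score. An arm difference that does not condition on it keeps between-person variation that could be removed, and in any one trial it moves with whatever baseline difference chance has produced. At stake is the width of the intervals around the harm-related outcomes that the intervention is meant to improve, in a sample where those intervals are already wide.

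**Working it through.** **The plan's own figures.** The article states no precision or power for these four outcomes. Its one sample-size figure concerns retention (69 of 100 kept gives a one-sided 95% lower bound above 60%). That reproduces: the exact lower bound is 0.605 at 69 and 0.595 at 68. It has no bearing on this point.

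**Inputs**
- 50 per arm randomised (Participants and Recruitment).
- 75% expected retention at week 6 (Primary Outcomes), so n = 0.75 × 50 = 37.5 per arm on average. No figure is given for weeks 12 and 18.
- Baseline to follow-up correlation ρ: not in the document. Assumed 0.3, 0.5 and 0.7.
- Outcome treated as continuous with the same SD at baseline and follow-up (assumption).

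**Formulas** (standard error of the arm difference, in SD units)
- Follow-up score only: √(2/n)
- Change score: √(2(1−ρ)) × √(2/n)
- Baseline-adjusted (ANCOVA): √(1−ρ²) × √(2/n) × √(1 + 1/(2n−3))

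**Numbers at n = 37.5.** √(2/37.5) = 0.231, so the half-width for the follow-up score alone is 1.96 × 0.231 = 0.45 SD. The small-sample factor is √(1 + 1/72) = 1.007.

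| ρ | Follow-up only | Change score | Baseline-adjusted |
|---|---|---|---|
| 0.3 | 0.45 | 0.453 × √1.4 = 0.54 | 0.453 × 0.954 × 1.007 = 0.43 |
| 0.5 | 0.45 | 0.453 × 1 = 0.45 | 0.453 × 0.866 × 1.007 = 0.39 |
| 0.7 | 0.45 | 0.453 × √0.6 = 0.35 | 0.453 × 0.714 × 1.007 = 0.33 |

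Leaving aside the small-sample factor, variance falls by ρ²: 9%, 25% and 49%. In sample-size terms that is 100/(1−ρ²), or about 110, 133 and 196 participants in place of 100.

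**Check by simulation** (20,000 runs, 37 per arm). The standard error was 0.232 SD for the follow-up score; 0.273, 0.233 and 0.181 for the change score; and 0.222, 0.203 and 0.168 for the adjusted estimate, in order of ρ. These agree with the formulas.

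**The same loss seen within one trial.** At 50 per arm the baseline difference has standard error √(2/50) = 0.20 SD, so it exceeds 0.20 SD in either direction in about 32% of randomisations. At 37.5 per arm the figure is about 39%. A 0.20 SD difference moves the unadjusted follow-up estimate by ρ × 0.20 = 0.06, 0.10 or 0.14 SD. In the simulation the adjusted estimate was uncorrelated with the baseline difference. Stratifying on CUD status will remove part of this in practice.

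**The case against.** The best defence is that method and aim agree. The aim is descriptive, the outcomes are exploratory, and the article attaches no test, interval or decision rule to them. Modelling is kept for the secondary outcomes and for satisfaction, which supports the acceptability assessment. That is a recognisable hierarchy and a defensible economy in a 100-person pilot. It explains the plan and lowers the severity. It does not remove the gain, because a descriptive estimate of an arm effect is also better when it is more precise.

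A reader might infer several stronger things that the document does not support:

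- *That the baseline is necessarily ignored.* Univariate analysis does not exclude change from baseline, and the article describes the Marijuana Problems Scale as measuring change over time. Only the cannabis-use end point is given as a level, in days per week. At ρ = 0.7 a change score recovers most of the gain (0.35 against 0.33 SD). At ρ = 0.3 it is worse than the follow-up score alone, and it is less precise than adjustment at every ρ shown.
- *That the estimates are biased.* Over randomisations they are not, and an ordinary unadjusted interval already allows for chance imbalance. Imbalance and lost precision are largely one loss, not two.
- *That power is lost.* No hypothesis test is planned for these outcomes, so power figures would describe an analysis that nobody proposes.
- *That the full trial's end point or size will be set on these estimates.* The article says only that results may inform later trials.
- *That clinical worsening would go unseen.* Adverse events are recorded and an independent data and safety monitoring board reviews accumulating data.

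**Conclusion.** The point holds as one of efficiency. For the Marijuana Problems Scale, days of cannabis use per week, the Severity of Dependence Scale and PANSS-6, the article states an analysis that makes less use of the collected baseline than it could. At about 37.5 per arm the 95% half-width would fall from about 0.45 SD to about 0.43, 0.39 or 0.33 SD at ρ = 0.3, 0.5 or 0.7.

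The size rests on an assumed ρ and on roughly continuous outcomes. At the low end of the range the gain is slight. The 75% retention is a week 6 figure. A different number at later visits would change the absolute widths but hardly the ratios between methods.

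Severity is low: exploratory outcomes, a pilot, an unadjusted estimate that is unbiased over randomisations, and no stated decision rule that depends on it.

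**What to change.** In the Statistical Analysis section, keep the univariate summaries by arm and visit. Add that, for the Marijuana Problems Scale, days of cannabis use per week, the Severity of Dependence Scale and PANSS-6, the arm difference will also be estimated from the model used for PBS and RCQ (arm, the outcome's own baseline score, site as a random effect), with the stratification factors sex and CUD status added. Fix these terms in advance, so that the own baseline score enters whether or not it happens to differ between arms. Report the adjusted difference with a 95% confidence interval at each post-baseline visit, or from one repeated-measures model per outcome, labelled exploratory and without a hypothesis test.

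The cost is small but not nil. Four outcomes at three visits make twelve fits, or four repeated-measures models. The covariate set is not identical to the one already planned for PBS and RCQ. Each model spends a few degrees of freedom. Days per week is bounded at 0 to 7, so its model needs a check of fit. No new data, visits or participants are needed, so the fact that enrolment has closed is no obstacle.

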### Data Collection and Management

Participation in the trial lasts up to 22 weeks, including up to 4 weeks between screening and randomization, 6 weeks of active CHAMPS intervention (immediate end point assessment), a booster session 4 weeks after the end of active CHAMPS intervention, and follow-up assessments conducted at weeks 12 and 18 (Table 2). Assessments are conducted either in person, over the phone, or using videoconferencing platforms. Communication and contact can be done digitally, over the telephone, or during in-person visits (only if confidentiality can be strictly maintained). All interactions are recorded in the patient study file. Furthermore, sites track participant interactions and collect information on recruitment, ineligibility reasons, and nonparticipation reasons. The research team uses these data to refine the recruitment strategy during the trial if needed.

**Table 2 table2:** Schedule of assessments.

Assessment name	Time point										
	Screening visit (week-4-2)	Baseline (W-2-W0)	Week 1	Week 2	Week 3	Week 4	Week 5	Week 6	Week 10	Week 12	Week 18
Screening form	✓										
Informed consent form	✓										
Locator form	✓							✓		✓	
Demographic questionnaire		✓									
Social Provision Scale-10		✓									
Readiness to Change Questionnaire		✓						✓		✓	✓
Marijuana Problems scale		✓						✓		✓	✓
Timeline Follow-back		✓						✓		✓	✓
Positive and Negative Syndrome Scale		✓						✓		✓	✓
Severity of Dependence Scale		✓						✓		✓	✓
Health care use		✓						✓		✓	✓
Randomization		✓									
Protective Behavioral Strategies—Marijuana		✓						✓		✓	✓
Client Satisfaction Questionnaire								✓		✓	
Adverse events								✓		✓	✓
Intervention and services form								✓		✓	✓

Data are entered into REDCap by site research staff or directly by the participant (through the CHAMPS app). The data dictionary will be built on REDCap and will be available upon request to the corresponding author. Final data quality assurance checks will be conducted by the data management team, and the study database will be locked, prohibiting further modification. The REDCap system was developed and implemented by the Center for Integration and Analysis of Medical Data to ensure that guidelines and regulations surrounding the use of computerized systems in clinical trials are upheld.

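### The PBS and RCQ models name site as the only random effect and no participant or visit term; if the three visits are stacked, the arm effect gets too narrow an interval and week 6 is pooled with later visits.

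*Protocol article*

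**What the plan says.** The Statistical Analysis section gives the PBS model as follows: "We will also conduct a hierarchical linear regression exploring the use of cannabis PBS over time as the outcome". It describes two steps: "the first regression model will insert study arms as the independent variable, and the second model will insert baseline PBS scores and other relevant covariates". RCQ is handled in the same way, "using hierarchical models that look at RCQ scores as the outcome and control for RCQ scores at baseline". On clustering it says: "In multivariable models, we will include sites as random effects". No participant-level random effect, within-person covariance, visit term or arm-by-visit term is mentioned.

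Data Collection and Management sets the timing: "6 weeks of active CHAMPS intervention (immediate end point assessment), a booster session 4 weeks after the end of active CHAMPS intervention, and follow-up assessments", the last of these being at weeks 12 and 18. Table 2 ticks both PBS and RCQ at baseline and at weeks 6, 12 and 18, so each person can contribute three post-baseline scores.

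On incomplete data, Statistical Analysis says: "Missing data will be handled issuing guidance of the missing data treatment for each instrument". It adds: "The proposed analyses will include all participants with at least 1 nonmissing visit".

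**The concern.** In this section, hierarchical means entering predictors in blocks. The same term and the same two-step description are used for the satisfaction comparison, so the word does not itself mean visits nested within people. Clustering is addressed, but at site level.

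The wording about PBS over time, the three scheduled visits and the inclusion rule of at least one visit all point to several rows per person in one model. Scores from one person at weeks 6, 12 and 18 are correlated. A model with a site intercept only would count them as separate pieces of information about the arm effect.

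The lack of visit terms is a second problem and does not depend on the size of that correlation. The booster falls at week 10, between the week-6 and week-12 assessments. A single arm coefficient would mix the effect at the end of the active intervention with scores taken after the booster, and could not show whether an early effect persists.

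The Secondary Outcomes section presents PBS and RCQ as the description and estimate of efficacy. Study Aims says an initial look at key clinical outcomes was needed before a large trial. In a pilot, much of the value of such an estimate lies in an honest statement of its uncertainty.

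**Working it through.** **The plan's own figure.** The only computed design figure in the article is in Sample Size: 69 retained of 100 for 95% confidence that true retention exceeds 60%. It reproduces. The exact 1-sided 95% lower bound is 60.5% for 69/100 and 59.5% for 68/100. The probability of at least 69 when the true rate is 60% is 0.040, against 0.062 for at least 68. The point made here does not touch this figure. The article gives no figure for PBS or RCQ.

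**Inputs from the article.** 100 participants, 1:1; 6 sites; 3 post-baseline visits; expected retention 75% (stated for week 6).

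**Assumptions.** The three visits are stacked in one model with a site intercept only. The within-person correlation ρ is not in the article, so a range is shown. Intervals are taken as 2-sided 95%, since none is specified for these outcomes.

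**Formulas, complete data, m = 3 visits.**
- Design effect for the average arm effect: DE = 1 + (m − 1)ρ = 1 + 2ρ.
- Reported width ÷ proper width = 1/√DE; coverage = 2Φ(1.96/√DE) − 1.
- After baseline adjustment, if baseline and follow-up scores share the same ρ, the residual correlation is (ρ − ρ²)/(1 − ρ²) = ρ/(1 + ρ). This replaces ρ in DE.
- For time or arm-by-time contrasts, reported width ÷ proper width = 1/√(1 − ρ).

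| ρ | DE | Width ratio, average arm effect | Coverage | Residual ρ after baseline | Width ratio after baseline | Width ratio, time contrasts |
|---|---|---|---|---|---|---|
| 0.1 | 1.2 | 0.91 | 92.6% | 0.09 | 0.92 | 1.05 |
| 0.3 | 1.6 | 0.79 | 87.9% | 0.23 | 0.83 | 1.20 |
| 0.5 | 2.0 | 0.71 | 83.4% | 0.33 | 0.77 | 1.41 |
| 0.7 | 2.4 | 0.65 | 79.4% | 0.41 | 0.74 | 1.83 |
| 0.8 | 2.6 | 0.62 | 77.6% | 0.44 | 0.73 | 2.24 |

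The first planned model contains arm without the baseline score, so the unadjusted columns apply to it. The time-contrast column uses the unadjusted ρ.

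**Check with dropout, by hand.** Assume (not from the article) that 80, 72 and 68 people attend weeks 6, 12 and 18, with no return after dropout. Then 8 people have one visit, 4 have two and 68 have three, giving 220 rows. With unit variance, the site-only SE is about 2/√220 = 0.135. The true variance is [220 + ρ(4×2 + 68×6)]/110² = (220 + 416ρ)/12,100.
- ρ = 0.5: √(428/12,100) = 0.188, so the ratio is 0.135/0.188 = 0.72.
- ρ = 0.7: √(511.2/12,100) = 0.206, so the ratio is 0.135/0.206 = 0.66.

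**Check by simulation.** 100 people, 6 sites, 3 visits, 25% of visits missing at random, no true effect, 250 runs per ρ, no baseline adjustment. The comparison model has a participant random intercept with site as a fixed effect.

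| ρ | SE, site only | SE, with participant | Ratio | Type I error, site only | Type I error, with participant |
|---|---|---|---|---|---|
| 0.3 | 0.135 | 0.163 | 1.20 | 7.6% | 3.6% |
| 0.5 | 0.134 | 0.177 | 1.32 | 14.0% | 6.4% |
| 0.7 | 0.134 | 0.190 | 1.41 | 19.2% | 4.8% |

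With 250 runs, the Monte Carlo standard error near 5% is √(0.05×0.95/250) = 1.4 percentage points, so the participant-model rates are compatible with 5%. The loss is smaller than with complete data because fewer rows per person are present.

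**The case against.** The strongest objection is that independence of visits is nowhere stated. The article says sites will be random effects; it does not say that nothing else will be. Secondary Outcomes speaks of change in PBS and in motivation, and the models adjust for baseline. Both would fit one model per visit or one change score, with one row per person and no within-person dependence. A condensed article may also leave the covariance structure to an analysis plan that is not shown. A reader might therefore infer that the trial will analyse repeated visits as independent and report intervals that are far too narrow. The documents do not support that as a fact; they support it only as the consequence of the natural reading of the text.

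Other parts of the objection also stand:
- ρ is assumed. At 0.1 the loss is small, and baseline adjustment reduces it throughout.
- The direction is not general: time contrasts would err the other way.
- The 75% expectation and 60% minimum in Primary Outcomes concern week-6 retention and are not dropout rates for all visits.
- It is an inference that instrument guidance covers missing items but not missed visits. The inclusion rule of at least one visit is also stated.
- No interval or test is promised for PBS or RCQ, and univariate summaries could still be shown by visit.

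What does not stand is the claim that this is mere silence. The section commits to an outcome over time, the predictors in each block and the level of clustering. An analyst following that text would have no participant or visit term to enter.

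**Conclusion.** The point holds conditionally. As written, the model for PBS and RCQ names site but no participant or visit term. If the three visits are stacked, the interval for the average arm effect has about 0.7 of its proper width at an assumed ρ of 0.5, within a range of 0.91 (ρ 0.1) to 0.62 (ρ 0.8). After baseline adjustment under equal correlations, the range is 0.92 to 0.73. Time and arm-by-time intervals would be too wide, by a factor of 1.41 at ρ 0.5. Whatever ρ is, one pooled arm coefficient joins week 6 to the visits after the booster.

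If the investigators intend a model per visit, a change score or a participant term, the variance problem does not arise and only the wording needs correcting. The consequence is limited to secondary, descriptive outcomes. A reader might go further and doubt the feasibility conclusions; retention and CHAMPS completion are single proportions with one value per person, so nothing here bears on them.

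**What to change.** Replace the blockwise description for PBS and RCQ with a linear mixed model for the week-6, 12 and 18 scores, fitted to all available visits:
- fixed effects: arm, visit, arm-by-visit, baseline score, and the two randomization strata (sex and CUD status);
- a participant random intercept or an unstructured within-person covariance;
- site, as already planned.

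Report the arm difference with a 95% interval at each visit, week 6 first and weeks 12 and 18 as supportive. Naming the strata in advance is also preferable to choosing covariates because they happen to differ at baseline. The likelihood fit uses people with some visits missing and is valid if data are missing at random, which should be stated as the assumption.

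The cost is a few sentences of analysis text and wider intervals. No data collection, sample size or primary analysis changes.

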#### Primary Outcomes

The feasibility of conducting a future RCT will be determined through the trial’s retention rate. The retention rate will be calculated by dividing the number of participants who completed all end point assessments (week 6) by the number of total randomized participants at baseline. As discussed, there are so far no other harm reduction–oriented studies in this population to guide our study design. Therefore, to establish an adequate minimum retention rate, we looked at related trials of (1) psychosocial mobile health interventions in populations with psychotic disorders, which had retention rates ranging from 76% to 100% [40-43] and (2) RCTs of face-to-face cannabis interventions for people with FEP, which had retention rates ranging from 52% to 96% [44-47]. The mobile health intervention trials either did not include comparison groups, did not focus specifically on individuals with FEP who used cannabis, or did not evaluate cannabis-focused interventions. The face-to-face interventions all focused on cannabis use in people with psychosis, but the delivery method precluded generalization to our trial. Given our intervention characteristics, we expect our retention rate will be on the lower end of these spectrums. We believe a 75% retention rate is a conservative estimate, but we are setting the minimum threshold for retention rate at 60%, which we believe represents a clinically important retention rate for our population.

Acceptability of the CHAMPS intervention will be assessed using the CHAMPS completion rate. This rate will be calculated by dividing the number of participants who completed at least the first 4 modules of CHAMPS by the number of total participants randomized to CHAMPS. We selected this completion threshold as the first 4 modules represent the core of the intervention, exposing participants to psychoeducation, motivational interviewing, personalized feedback, and skills training.

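### Choosing model covariates by observed baseline difference will usually leave out sex and CUD status, the two factors that randomization was stratified on

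*Protocol article*

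**What the plan says.** Under Randomization and Blinding, allocation is 1:1 and "Randomization is stratified by sex and CUD status using random permuted blocks". The block size is not given.

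Under Statistical Analysis, satisfaction, PBS and RCQ are each modelled in two steps. The first step contains study arm. The second adds covariates, with the baseline score fixed for PBS and RCQ; satisfaction has no baseline measurement. The rule for all the multivariable models is "In multivariable models, we will include sites as random effects and will include certain covariates of interest that differ at baseline". The candidates are then listed conditionally: "These covariates may include age, sex, gender, study site, education status, employment, housing status, social support, and baseline clinical characteristics", the last group covering cannabis use and CUD severity. No criterion for a difference is given (p-value, standardised difference or judgement), and nothing commits the models to the stratification factors. CUD status, the factor actually used to stratify, is not on the list by that name.

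**The concern.** The two sections pull against each other. Stratified blocks exist to make the arms alike on sex and CUD status; a rule that admits only covariates on which the arms are unlike will tend to omit exactly those factors. Yet the gain from stratifying reaches the stated precision only if the analysis contains the factors. If they are prognostic and left out, the model charges their variance to error although the design has already removed it from the comparison.

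In a randomized trial, baseline differences arise by chance, and their size does not show whether a variable predicts the outcome. The rule therefore also lets in covariates for a reason unrelated to their usefulness, after the data have been seen. At stake is the precision of the PBS, RCQ and satisfaction estimates in a pilot meant to precede a larger trial.

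**Working it through.** The plan gives no figure on this point. Its one computed figure, 69 of 100 retained, reproduces (exact one-sided 95% lower bound 60.5%) but has no bearing here.

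**Inputs from the protocol article.** 100 randomized, 50 per arm (Participants and Recruitment); 1:1 permuted blocks within sex and CUD status (Randomization and Blinding); retention 75% expected, 60% minimum (Primary Outcomes).

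**Assumptions, not in the article.** Block sizes 4, 6 and 8; prevalences of the two factors 0.75/0.60, 0.80/0.80 and 0.50/0.50; share R² of outcome variance explained by the strata; outcome–baseline correlation 0.5.

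**1. How often would the rule select a stratification factor?** Simulation, 4,000 trials per setting:

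| Criterion | All randomized | Completers, 25% dropout | Completers, 40% dropout |
|---|---|---|---|
| p < 0.05 | 0.0% | at most 0.3% | at most 0.7% |
| standardised difference > 0.2 | at most 1.6% | 10–17% | 24–30% |

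An unstratified binary covariate, checked in all randomized participants, meets p < 0.05 in about 5% of trials and a standardised difference above 0.2 in about 34%.

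**2. How often does chance admit something else?** Apart from sex and site, the list names eight candidates: age, gender, education, employment, housing, social support, cannabis use and CUD severity. Treated as independent and screened at p < 0.05, at least one enters with probability 1 − 0.95⁸ = 0.34. A simulation gave about 33%.

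**3. What does omitting the strata cost?** With outcome variance 1 and balanced strata, the ratio of standard errors (without/with strata) is the square root of the ratio of residual variances.

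- *No baseline score (satisfaction).* Ratio = 1/√(1 − R²) = 1.054, 1.118 and 1.195 for R² of 0.1, 0.2 and 0.3. Simulation at 75% retention gave 0.231/0.220 = 1.05, 0.230/0.207 = 1.11 and 0.231/0.194 = 1.19.
- *Baseline score in the model, strata acting equally on baseline and follow-up (PBS, RCQ).* With overall correlation 0.5, residual variance without strata is 1 − 0.25 = 0.75. Within strata the correlation is r = (0.5 − R²)/(1 − R²) = 0.444, 0.375, 0.286, so residual variance with strata is (1 − R²)(1 − r²) = 0.722, 0.688, 0.643. The ratios are √(0.75/0.722) = 1.019, √(0.75/0.688) = 1.044 and √(0.75/0.643) = 1.080. Simulation gave excesses of about 1.5, 4 and 7%. If 0.5 is instead the within-stratum correlation, the simulated pairs 0.194/0.191, 0.186/0.181 and 0.177/0.169 give about 2, 3 and 5%.
- *Baseline score in the model, strata predicting follow-up only.* Ratio = √(0.75/(0.75 − R²)); at R² = 0.1 this is √(0.75/0.65) = 1.074. Simulation of the selection rule against the strata model gave 0.203/0.189 = 1.074.

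**4. Are the intervals valid?** This is a separate question from step 3: model standard error against the true sampling SD. In the follow-up-only case with 25% dropout, the rule overstates the SD by about 3% at R² = 0.02 and 11% at R² = 0.20, with coverage of 95.6% and 97.1%. With sex, CUD status and baseline score prespecified, coverage was 94.7–95.6% over the settings run. With the baseline score carrying the strata effect (the second case in step 3), type I error without strata was 4.4–4.9%. Departures are on the conservative side.

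**The case against.** Several points on the other side are sound.

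- **The size depends on the baseline score.** A reader might take the 5 to 19% range to apply to all three models. It does not: the article fixes baseline PBS and RCQ in their own models, and those scores may already carry much of the strata effect. The range belongs to satisfaction.
- **Exclusion is not certain.** A reader might infer that the stratification factors can never enter. That holds nearly always for a p-value criterion or a check in all randomized participants, but the article fixes neither; a standardised difference among completers would admit them in a minority of trials. Sex and CUD severity are also named as candidates. A conditional list still guarantees nothing, and severity is not the stratification variable.
- **Analyst freedom is bounded.** The arm-only first step is fixed for each outcome, the candidate list is published, and those analysing the data are blinded to group. This limits steering of the result but does not make the selection rule a good one.
- **Power.** A reader might want a power loss. The article states no effect size or between-arm power target, and its secondary objectives are descriptive, so no power figure can be tied to it.
- **Site.** Its appearance both as a random effect and among the candidates reads as loose drafting, not as a commitment to fit both.

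Final covariate sets are often left to the analysis plan. Here, however, the article states a selection rule, and the point is that rule, not missing detail.

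**Conclusion.** The point stands at modest size. The stated rule works against the stated design: it will usually omit sex and CUD status and admits other covariates on chance imbalance. If the strata explain 10 to 30% of outcome variance, the standard error of the arm effect is larger than with strata adjustment by about 1.5 to 7% for PBS and RCQ when the baseline score carries the strata effect, and by about 5 to 19% for satisfaction. It can be larger for PBS and RCQ if the strata predict follow-up but not baseline. If they are not prognostic, the loss is negligible. The article does not say how prognostic they are, so these ranges rest on assumption.

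A reader might infer false-positive findings or a threat to the trial's main conclusions. Neither is supported: the error is conservative, and retention and completion are reported by univariate analysis without these models.

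**What to change.** Replace the covariate sentences under Statistical Analysis with a fixed specification: each adjusted (second-step) model for satisfaction, PBS and RCQ contains arm, sex and CUD status as used in the randomization, and the baseline value of the outcome where one exists (PBS and RCQ), with site as a random effect only. Delete the baseline-difference criterion and remove site from the candidate list. Name any further covariates in advance, on prognostic grounds.

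Cost: two degrees of freedom per model. No new data are needed, since both factors are recorded for randomization.
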